### Occlusion dose monitoring

All study participants who progress to the occlusion phase have their prescribed patch wear (standardized or personalized dosing strategy) objectively monitored using an occlusion dose monitor. Briefly, this device monitors, and records electronically, episodes of patch-skin contact indicative of patch wear. At the scheduled clinic visits, the occlusion dose monitor is interrogated via a PC to provide a time history of patching episodes from which daily (‘dose-rate’) and accumulated (‘dose’) occlusion can be derived. A full description of the occlusion dose monitor’s construction and mode of operation has been reported elsewhere [9,10].

### Endpoint determination and sample size calculation

Participants complete the trial at that point in the occlusion phase at which equal visual acuity of each eye is achieved, or if vision has stabilized (defined as three inflexions in a plot of acuity against time or remaining unchanged over three consecutive visits). All children wear occlusion for a minimum of 6 weeks before discontinuing if no significant gains in visual acuity are observed. A sample size of 60 in each arm at 95% power and with a type I error rate of 0.05 corresponds to a Cohen’s *d* statistic of 0.605. The log-transformed time to best visual acuity across MOTAS [11] and ROTAS [12] was approximately normally distributed and had a mean (standard deviation) of 4.0133 (0.801). We could therefore expect to detect a difference of around 21 days in mean time to best visual acuity in our two groups.

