A practical consequence of this research has been a trend away from *ad-hoc* patching regimens (anything from a few minutes per day up to all waking hours) towards a more standardized approach (now gradually being incorporated into practice guidelines [14]). Thus, it is now possible to elicit consensus among expert practitioners as to what presently constitutes best practice, that is, in the amount of patching that should be prescribed to an initially presenting amblyopic child. In this Randomized Occlusion Dosing Strategies (RODS) trial, the occlusion regimens prescribed in one of the treatment arms (the standardized dosing strategy) represents the current prevailing clinical opinion of a representative group of UK orthoptists.

The rationale behind RODS is the notion that further refinements in prescribing may yield improvements in outcome. By examining the dose-response relationships determined for the amblyopic children taking part in MOTAS [11] and ROTAS [12], we have generated a statistical model that allows us to estimate, on the basis of the severity of the initially presenting amblyopia, the age of the patient, and the type of amblyopia, the amount (total hours) of occlusion required to treat any given amblyopic child. This we term the ‘total effective dose’, which for any given treatment period can be converted into a daily dose-rate (hours per day) and subsequently increased or decreased depending on compliance. We term this approach a ‘personalized dosing strategy’.

In summary, the protocol described herein has been designed to test the hypothesis that superior clinical outcomes will be obtained with a personalized dosing strategy compared with a standardized dosing strategy (in which all patients receive an occlusion regimen based upon current best practice).

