#### Occlusion phase

On entering this phase, study participants are randomly assigned (stratified by geographic site and amblyopia type) to either the personalized or standardized dosing strategy arms of the trial using an online true random number generator [16].

Participants will have their visual acuity recorded every 2 weeks until the trial endpoint is reached. To provide a check against the unmasked nature of the study design, visual acuity is further recorded at the end of the occlusion phase by an examiner masked to the participants’ treatment arms.

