#### Analyses

The primary study objective of comparing time to best visual acuity between the two treatment groups, along with the secondary objective of comparing compliance, will be analyzed via standard *t* tests (to compare length of time and compliance) and Levene’s test (to compare variance in time). Suitable nonparametric alternatives will be used should concerns arise regarding the necessary distributional assumptions for these methods. The secondary objective to determine the relationship between changes in visual acuity and dose, amblyopia type, and age, will be investigated using standard regression modelling approaches.

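### The primary time comparison counts a child who plateaus without gain as a completed, relatively short time, and no listed analysis compares acuity between the arms

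*Protocol article*

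**What the plan says.** All references are to the Protocol article.

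- **Exit rule** (Endpoint determination and sample size calculation). A child completes the trial when "equal visual acuity of each eye is achieved, or if vision has stabilized (defined as three inflexions in a plot of acuity against time". The first route is success. The second is a plateau, which in full reads "or if vision has stabilized (defined as three inflexions in a plot of acuity against time or remaining unchanged over three consecutive visits". The second route asks for no improvement. The same section foresees children who do not improve: "All children wear occlusion for a minimum of 6 weeks before discontinuing if no significant gains in visual acuity are observed".
- **Visits** (Occlusion phase): "Participants will have their visual acuity recorded every 2 weeks until the trial endpoint is reached".
- **Objective** (Objectives of the study). The aim is to reach the trial endpoint sooner and with less variance, and that endpoint is equated with optimal acuity.
- **Hypothesis** (Background): "superior clinical outcomes will be obtained with a personalized dosing strategy compared with a standardized dosing strategy".
- **Primary outcome** (Primary outcome and its measurement). LogMAR visual acuity is named the primary outcome variable.
- **Analyses.** "The primary study objective of comparing time to best visual acuity between the two treatment groups" is to be done by t test. Variance of time is compared by Levene's test and compliance by t test. The only acuity analysis regresses change in acuity on dose, amblyopia type and age; treatment arm is not among the listed terms.
- **Masked measurement** (Occlusion phase): "visual acuity is further recorded at the end of the occlusion phase by an examiner masked to the" treatment arm. Its stated purpose is to check on the unmasked design. No between-arm analysis is attached to it.

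**The concern.** Time to an endpoint measures benefit only if reaching the endpoint means the same thing for every child. Here it can mean equal acuity in both eyes, a plateau after partial gain, or a plateau with no gain. The t test does not separate these. A child who never improves can meet the stabilization rule near the minimum treatment period and, if time means time to best acuity, may score earlier still. A child who improves steadily to equal acuity over 12 weeks scores 84 days.

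If the arms differ in the proportion who do not improve, the arm with more of them gains an advantage on the primary comparison. Because no listed analysis compares acuity by arm, the results as planned would not show whether a shorter time came with the same vision or with worse vision.

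**Working it through.** **Inputs from Endpoint determination and sample size calculation:** log time to best acuity, mean 4.0133 and SD 0.801; d = 0.605; 60 per arm; 6-week minimum (42 days) without gains. **From Occlusion phase:** first follow-up visit at 14 days. **Assumed, because the documents give no rate:** one arm has an excess f of non-improvers, f = 0.10 or 0.20, and the remaining children follow the stated distribution.

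**1. The plan's own figure.** Geometric mean time = exp(4.0133) = 55.3 days. A shift of 0.605 × 0.801 = 0.485 on the log scale gives exp(4.0133 − 0.485) = 34.1 days. The difference is 55.3 − 34.1 = 21.2 days, so the stated 21 days reproduces as a difference of geometric means.

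**2. Effect of excess non-improvers.** If they are scored at day t, mean log time shifts by f × (ln t − 4.0133), the geometric mean is multiplied by the exponential of that shift, and the fall in days is 55.3 × (1 − ratio).

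| Scoring of non-improvers | f | Shift | Ratio | Fall in days |
|---|---|---|---|---|
| Day 42 (exit at the minimum) | 0.10 | 0.10 × (3.738 − 4.0133) = −0.028 | 0.973 | 1.5 |
| Day 42 | 0.20 | −0.055 | 0.946 | 3.0 |
| Day 14 (best acuity at first visit) | 0.10 | 0.10 × (2.639 − 4.0133) = −0.137 | 0.872 | 7.1 |
| Day 14 | 0.20 | −0.275 | 0.760 | 13.3 |

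An intermediate case has the best reading equally likely at days 14, 28 or 42. Mean log time is then (2.639 + 3.332 + 3.738)/3 = 3.236. For f = 0.20 the shift is 0.20 × (3.236 − 4.0133) = −0.155, the ratio 0.856 and the fall about 8 days.

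**3. Effect on the test.** Simulation: 60 per arm, two-sided 5% t test on log time, fortnightly visits, improvers drawn from the stated distribution identically in both arms, 10% non-improvers in one arm. The arm with 20% or 30% non-improvers is declared significantly faster in about 6% or 10% of trials when they are scored at day 42, and in about 16% or 46% when scored at day 14. The nominal rate in that direction is 2.5%.

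**4. Which routes matter.** If inflexions are read as turning points, three of them need at least five readings. With the starting reading counted, that is 4 × 14 = 56 days at the earliest, no earlier than the 55.3-day mean. On the time-to-exit reading, the early route is therefore unchanged acuity over three visits, limited by the 6-week minimum. Since 42 is below 55.3, the direction of the bias remains.

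**The case against.** **The protocol assumes the arms differ in time and not in final acuity.** Under Personalized dosing strategy, each child has a fixed optimal acuity, reached once the total effective dose is received. If that held and every child received that dose, the concern would fall away. But the same section says improvement is limited when the dose falls short, and the Discussion reports received occlusion at less than half of that prescribed. Incomplete response is foreseeable on the protocol's own account.

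**The 6-week minimum limits the bias.** This stands. With time read as time to exit, a 20-point excess moves the geometric mean by only about 3 days.

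**There are partial safeguards.** Compliance is compared by arm, acuity change is modelled on monitored dose, and masked acuity is recorded. These would give hints, but none is a comparison of acuity by arm.

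**An acuity comparison may sit in an analysis plan that is not shown.** That is possible, and its absence alone would be no finding. The article does, however, state the primary comparison, its test and its sample size, and these disagree with its own named outcome variable and hypothesis. A plan that followed the Analyses section would carry the problem forward.

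**A reader might infer that non-improvers score at day 0.** On the raw scale, with an arithmetic mean of exp(4.0133 + 0.801²/2) = 76.3 days, a 20-point excess would then remove 0.20 × 76.3 = 15 days. The documents do not support this: they do not say how time is scored for a stabilized child, day 0 has no logarithm, and with letter-by-letter scoring a non-improver's best reading may fall at any visit by chance.

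**Conclusion.** The concern holds. As written, stabilization without gain counts as reaching the endpoint, the primary test takes that time at face value, and no listed analysis compares acuity between arms. The Background, Objectives, Primary outcome and Analyses sections do not agree on what success is.

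The direction is clear: more non-improvers in an arm shorten its mean time. The size is not known. It runs from about 3 to 13 days for a 20-point excess and from about 1.5 to 7 days for a 10-point excess, against a planned difference of 21 days. It depends on an assumed excess and on whether time means exit or best acuity, which the article does not settle.

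A reader might go further and conclude that a worse regimen will be declared superior, or that most of the planned effect could be artefact. The documents do not support that: they give no non-improver rate and no reason to say which arm would have more, and the larger figures need the most extreme scoring.

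**What to change.** 1. Reconcile the Background, Objectives of the study, Primary outcome and its measurement, and Analyses on one primary outcome, and state whether time runs to exit or to best acuity.
2. Add to Analyses a between-arm comparison of the masked end-of-phase acuity of the amblyopic eye, by ANCOVA adjusted for acuity at the start of occlusion. Report it with its 95% confidence interval beside the time result, and interpret a shorter time as benefit only in the light of it.
3. As a supportive analysis, report the cumulative incidence of equal acuity by arm, with stabilization without equal acuity as a competing event.

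Any formal non-inferiority margin is for the sponsor to justify. The 0.10 logMAR in Optical treatment phase is a within-child threshold for extending spectacle wear, not a between-arm margin, and gating the claim on it would change the trial's success rule. For scale, with 60 per arm and truly equal acuity, the chance of excluding a 0.10 deficit is Φ(0.10/(SD × √(2/60)) − 1.96): about 95%, 78% or 59% for an assumed adjusted SD of 0.15, 0.20 or 0.25.

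The cost is small. The masked measurement is already scheduled, and the exit rule and treatment are untouched. The downside is a little more analysis, and a time advantage may be harder to call superior.

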### Outcomes and analyses

#### Primary outcome and its measurement

The primary outcome variable is logMAR visual acuity assessed on one or more of the following test charts: crowded logMAR, uncrowded logMAR, or modified ETDRS.

The crowded and uncrowded logMAR charts are viewed at a test distance of 3 m and comprise six letters, X V O H U Y, which were selected for their approximately equal legibility. There are four letters on each line, which provide a constant visual demand at each level of acuity. Each letter correctly read can be scored by interpolation as 0.025 logMAR with an acuity range of 0.800 to −0.300 logMAR (6/38 to 6/3), which can be extended to 1.4 to −0.300 logMAR by employing a log increment step reduction in viewing distance. Letter spacing is equal to 0.5 letter diameters. In the crowded chart, a black printed rectangle surrounds each row of letters at 0.5 letter diameters distance and of equivalent width to the letter height.

The modified ETDRS chart is viewed at a test distance of 4 m, giving an acuity range of 1.00 to −0.30 logMAR (6/60 to 6/3). This test range can be extended to 1.60 logMAR by reducing the viewing distance in log incremental steps. Each line comprises five letters and is scored on a letter-by-letter basis, providing interpolated acuity values of 0.02 logMAR resolution.

The chart used depends on the reading ability of the child and is generally age-dependent. The visual acuity test used in the initial assessment phase will be used throughout the trial period; however, if a child is judged able to progress to a more difficult test, this test will additionally be employed for the remainder of the trial. Visual acuity of the amblyopic eye is always recorded first; the rationale being that amblyopic eye visual acuity is the principal outcome variable and the visual acuity of this eye should be tested when the child is maximally alert and free of fatigue.

#### Analyses

The primary study objective of comparing time to best visual acuity between the two treatment groups, along with the secondary objective of comparing compliance, will be analyzed via standard *t* tests (to compare length of time and compliance) and Levene’s test (to compare variance in time). Suitable nonparametric alternatives will be used should concerns arise regarding the necessary distributional assumptions for these methods. The secondary objective to determine the relationship between changes in visual acuity and dose, amblyopia type, and age, will be investigated using standard regression modelling approaches.

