## Methods/design

### Objectives of the study

The primary study objective is to determine whether study participants in receipt of a personalized dosing strategy reach trial endpoint (optimal visual acuity) in a shorter period of time, and with reduced variance, than those in receipt of a standardized dosing strategy.

The secondary study objectives are:To determine the relationship between observed changes in logMAR visual acuity as a function of:Objectively monitored occlusion dose,Type of amblyopia,Age of participant.To determine whether compliance differs between standardized and personalized dosing strategy treatment arms.

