Predictions of *D*_*i*_^***^ were derived from a normal linear interval regression model with the total effective dose of some patient *i* with initial residual amblyopia *R*_*i*_ and age *A*_*i*_ estimated by the formula:$$ {\mathrm{D}}_{\mathit{\mathsf{i}}}^{*}={\left(18.150+16.122{R}_i\hbox{--} 0135{A}_i\hbox{--} 0.547{T}_M\hbox{--} 8.028{T}_S\hbox{--} 12.176{R}_i{T}_M\hbox{--} 11.334{R}_i{T}_S+0.065{A}_i{T}_M+0.192{A}_i{T}_{\mathrm{S}}\right)}^2 $$where *T*_M_ and *T*_S_ are indicator functions taking the value 1 if the patient has mixed or strabismic amblyopia, respectively, or 0 otherwise.

In practice, participants in the personalized dosing strategy arm have their total effective dose estimated on an assumed fixed follow-up period of 12 weeks, which results in manageable dose-rates. Therefore, an individual patient’s personalized daily patching regimen will be calculated by first estimating the total effective dose and then dividing this by the number of days left in the follow-up period. For reasons of practicality, we only prescribe daily patching episodes rounded up to the nearest 30 minutes. Dose-rate can then be updated at follow-up appointments based on how much occlusion has been objectively recorded. To avoid the prescription of subtherapeutic doses of occlusion, the model is constrained such that dose-rates less than 2 hours per day are never prescribed. Of course, patients will probably be treated for a period longer than 12 weeks, as the follow-up sessions will be continued until the visual acuity criteria for study exit have been met. Therefore, once a patient passes the tenth week of follow-up, all future daily prescription calculations will assume a 2-week follow-up period until treatment is completed.

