### Trial status

Participant enrolment commenced in October 2013 and the trial is scheduled to complete by December 2015.

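### The primary t test on time has no place for a child who leaves the occlusion phase before meeting an exit criterion; use a censored time model instead

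*Protocol article*

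**What the plan says.** The primary objective (Objectives of the study) is whether children on personalized dosing "reach trial endpoint (optimal visual acuity) in a shorter period of time, and with reduced variance". The section Endpoint determination and sample size calculation gives two ways to finish. The first reads: "Participants complete the trial at that point in the occlusion phase at which equal visual acuity of each eye is achieved". The second is a stable acuity, which the same section specifies as "three inflexions in a plot of acuity against time or remaining unchanged over three consecutive visits".

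Follow-up is open-ended. The Occlusion phase section states: "Participants will have their visual acuity recorded every 2 weeks until the trial endpoint is reached". The Personalized dosing strategy section adds that "the follow-up sessions will be continued until the visual acuity criteria for study exit have been met". No maximum duration is given.

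The Analyses section assigns the comparison of time to best visual acuity to standard t tests ("to compare length of time and compliance") and Levene's test for variance. The only stated fallback is: "Suitable nonparametric alternatives will be used should concerns arise regarding the necessary distributional assumptions for these methods". The sample size calculation uses 60 children per arm and states no allowance for loss.

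**The concern.** A time to endpoint with open-ended follow-up is complete only for children who reach the endpoint. A child whose family withdraws during occlusion, or who is unfinished if follow-up is stopped, contributes only the fact that the endpoint lies beyond the last visit. A t test needs one number per child and cannot use that fact. Nor can an ordinary rank test, and the fallback is triggered by distributional shape, not by incomplete times.

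The analyst then has two routes. Assigning a time, such as the last recorded visit, makes the child look fast. Excluding the child removes long times preferentially, because slow responders have longer in which to leave. If loss differs between arms, either route can produce a difference that is not there. If loss is equal, precision is lost and a true difference can be diluted.

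Some loss is plausible. The Discussion calls occlusion unpleasant and reports recorded wear below half of what is prescribed. Only the personalized arm has its prescription recalculated from recorded wear, so loss could differ by arm, although the documents do not show that it would, or in which direction.

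**Working it through.** **Inputs from the article (Endpoint determination and sample size calculation).** Log time in days: mean 4.0133, SD 0.801. 60 per arm, Cohen's d 0.605, type I error 0.05, power 95%, detectable difference about 21 days. Visits every 2 weeks (Occlusion phase).

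**1. The plan's own figures.** The effect on the log scale is 0.605 × 0.801 = 0.4846, a time ratio of exp(−0.4846) = 0.616. The geometric mean is exp(4.0133) = 55.3 days, and 55.3 × (1 − 0.616) = 21.2 days, so the 21 days reproduce. With the noncentral t distribution, 60 per arm gives 95.1% power one-sided and 90.8% two-sided. The stated 95% therefore holds for a one-sided 0.05 test; sidedness is not stated. The figures below use a two-sided 0.05 test, so the starting power is about 90%. Both power figures assume an observed time for all 60 children in each arm.

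**2. Are long times expected?** Under the plan's distribution, P(T > 84 days) = 1 − Φ((ln 84 − 4.0133)/0.801) = 1 − Φ(0.521) = 30%. P(T > 180 days) = 1 − Φ(1.473) = 7%. A sizeable minority would be in treatment long enough to be at risk of leaving first.

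**3. Simulation.** Times are drawn from the plan's log-normal and rounded up to 14-day visits, with 60 per arm and a t test on log time. Drop-out is assigned at random to a stated fraction of each arm, at a time uniform over a window. A child counts as unfinished only if drop-out comes before the endpoint, so 10% and 30% assigned leave about 7% and 21% unfinished when the window is days 0 to 84. Rates and windows are assumptions; the article gives none.

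*No true difference, 10% (standardized) v 30% (personalized) assigned. Trials declaring personalized faster, nominal 2.5%:*

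| Drop-out window | Last recorded time used | Unfinished children excluded |
|---|---|---|
| Days 0–84 | about 24% | about 7% |
| Days 28–168 | about 6% | about 6% |

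*Equal loss, no true difference:* the error rate stays at its nominal level.

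*Planned effect, 20% to 30% assigned in both arms:* power falls from about 90% to between 67% and 88%. It is lowest with 30% early loss and recorded times, and highest with 20% late loss.

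**4. A simpler variant as a check.** Without rounding to visits, and with drop-out in days 14 to 84:
- 10% v 30% assigned, no true difference: two-sided error of 10.5% (stop time used) or 6.3% (excluded), against 5%.
- 20% assigned in both arms: error about 5%, and the 21.2-day effect reads as 19.7 days (stop time used) or 20.9 days (excluded), with power 87% either way.

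The direction agrees with step 3; the size depends on the coding and timing of loss.

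**The case against.** The strongest reply is that this is a condensed article, and the handling of withdrawals normally sits in a full protocol or analysis plan that is not shown. That is right as far as it goes: silence on withdrawals is not the point. But the article does choose the primary test, and a censored-data method elsewhere would replace that choice. Imputation could keep the t test, but a sound imputation needs a model for the censored times, which would then do the real work.

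Four stronger readings are tempting and not supported.

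- A reader might infer that unfinished children are counted as early finishers or dropped. The article states no rule; the t test only forces some such choice.
- A reader might include children who stop patching. If they keep attending and exit under the stabilization rule, their endpoint is observed. A censored model would count them as events too, so they lie outside this point.
- A reader might take the statement that "the trial is scheduled to complete by December 2015" as a cut-off for follow-up. It is a schedule. No date of last randomization is given, so whether any child would be unfinished then cannot be determined. Withdrawal alone is enough for the point.
- A reader might conclude that the comparison is biased. Bias depends on the amount, timing and balance of loss, none of which is given.

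It is also fair that a censored model is no cure-all. It assumes non-informative censoring. When slower children were made likelier to leave (10% v 45% assigned, days 14 to 84, 150 runs), the model gave a time ratio of about 0.91 with no true difference. That caveat stands and is carried into the fix.

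**Conclusion.** The point holds in a limited form. The stated primary test does not suit a time outcome with open-ended follow-up, because it cannot use the right-censored time of a child who meets no exit criterion. The false-positive range of about 6% to 24% (nominal 2.5%) requires loss that differs between arms. The power range of 67% to 88%, from about 90%, applies to equal assigned loss of 20% to 30%. Both rest on the plan's log-normal distribution, a two-sided 0.05 test, and assumed loss that is unrelated to response. With little or no loss the t test would do no harm. The change is worth making because it is cheap and protects the primary comparison whatever the loss turns out to be.

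**What to change.** In the Analyses section, make the primary time comparison a log-normal time model fitted by interval regression:

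- **Population:** all randomized children, in their assigned arm.
- **Censoring:** children who meet no exit criterion are right-censored at their last acuity visit.
- **Event interval:** matched to the named variable. For time to best acuity, it ends at the visit at which best acuity was first recorded. For stabilization exits this is not the interval between the last two visits.
- **Variance objective:** an arm-specific scale parameter in the same model, or Levene's test kept as supportive.
- **Reporting:** Kaplan-Meier curves by arm, and the number unfinished by arm and reason.
- **Sensitivity:** the t test as now stated, and an analysis allowing drop-out to be related to slow response.

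This keeps the planning distribution and uses the same class of model the team already used to predict total effective dose. The cost is a few sentences, with no new data or patients. The downside is a model-based time ratio in place of a simple mean difference, resting on non-informative censoring; the last sensitivity analysis is there to test that.

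### The sample size is built on log time, but the t test and Levene's test read as applying to time itself, where a smaller variance largely restates a shorter mean

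*Protocol article*

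**What the plan says.** Under Objectives of the study, the primary objective has two parts: the personalized arm should reach endpoint "in a shorter period of time, and with reduced variance".

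Under Endpoint determination and sample size calculation, planning is on the log scale: "The log-transformed time to best visual acuity across MOTAS [11] and ROTAS [12] was approximately normally distributed", and it "had a mean (standard deviation) of 4.0133 (0.801"). The design is described as "A sample size of 60 in each arm at 95% power and with a type I error rate of 0.05", corresponding to a Cohen's *d* "statistic of 0.605", and this is converted to about 21 days.

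Under Analyses, the methods are *t* "tests (to compare length of time and compliance") and Levene's test ("to compare variance in time"). Neither a scale nor a centring for Levene's test is given. A fallback follows: "Suitable nonparametric alternatives will be used should concerns arise regarding the necessary distributional assumptions for these methods". It names no test and no trigger.

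**The concern.** The planning and analysis sections appear to use different scales for the same primary quantity. For the comparison of time, this means the stated power belongs to a test other than the one named. For the comparison of variance it matters more. If a treatment shortens times by a constant factor, it shrinks the SD in days by that same factor, even when children within each arm are just as variable in relative terms. A significant Levene's test in days could then be reported as meeting the second half of the primary objective, and read as personalized dosing making treatment duration more predictable, when it only repeats that duration was shorter.

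**Working it through.** **Inputs from the article.** 60 per arm; power 95%; alpha 0.05 (sidedness not stated); d = 0.605; log time with mean 4.0133 and SD 0.801.

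**Assumptions.** The standardized arm has log mean 4.0133. Both arms have log SD 0.801 (the article gives one pooled historical value). Personalized dosing shifts log time only.

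**1. Reproduce the plan's figures.**
- Noncentral *t*, 60 per arm: the d detectable with 95% power is 0.604 at one-sided 0.05 and 0.664 at two-sided 0.05. So 0.605 reproduces one-sided (power 95.1%). Two-sided, power at 0.605 is 90.8%.
- Shift on the log scale: 0.605 × 0.801 = 0.4846. Time ratio: exp(−0.4846) = 0.616.
- Days: exp(4.0133) = 55.3, and 55.3 × (1 − 0.616) = 21.2.

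The 21 days is therefore a back-transformed difference of geometric means. Both d and the 21 days come from the log scale.

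**2. What the same model implies in days.**
- Arithmetic mean, standardized arm: exp(4.0133 + 0.801²/2) = 76.3. Personalized arm: 76.3 × 0.616 = 47.0.
- Coefficient of variation: √(exp(0.801²) − 1) = 0.95 in both arms.
- SDs: 72.3 and 44.5 days. Variance ratio: 0.616² = 0.38, although the log SDs are equal.

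**3. Behaviour of the tests.** Simulated log-normal trials, 60 per arm, at least 20,000 replicates. Levene's test is two-sided at 0.05.

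| Scenario (equal log SDs) | Levene on days, mean-centred | Levene on days, median-centred | Levene on log time, mean / median |
|---|---|---|---|
| Planned shift (ratio 0.616) | 63–64% | 48% | about 5% / 5% |
| Ratio 0.8 | 28% | 14% | about 5% / 5% |
| Identical arms | 15–16% | 5% | about 5% / 5% |

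| Test of time at the planned shift | One-sided power | Two-sided power |
|---|---|---|
| t test on log time | 95% | 91% |
| t test on days | 88% | about 81% |
| Mann-Whitney | 94% | about 89% |

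Welch's version of the raw t test gives the same power as the standard one.

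**4. The fallback applied to variance.** Under the planned shift with equal log SDs, Fligner-Killeen on days rejects in about two thirds of trials, Mood's test in about 3 to 4%, and Levene's test on pooled ranks in about 1 to 3%. All three could be called suitable nonparametric alternatives, and they answer the variance question differently.

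**The case against.** A reader might infer that the plan expressly specifies untransformed time. It does not. That is the plain reading of Analyses, but the only distributional statement in the article favours logs, and a log-scale t test may have been intended. This stands, and it makes the point one of alignment rather than a demonstrated wrong choice.

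A reader might also infer that the trial simply loses its planned power. The fallback clause weakens that. Log-normal times with this SD fail a Shapiro test in essentially every arm of 60, so a normality check would very probably trigger the switch, and Mann-Whitney gives up only about one to two points against the log-scale t test. This stands for the comparison of time. The clause covers Levene's test too, but because no alternative is named it does not settle the variance question.

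Three further readings go too far:
- *Levene's test is badly oversized when the arms are identical.* The 15–16% belongs to mean centring, which the article does not name. Median centring holds its level.
- *A positive Levene result in days would be false.* Under the planning model the variance in days really is smaller. The error lies in reading it as an effect separate from the shorter time.
- *The trial has only about 48% power for its primary objective.* That needs a rule that both tests must succeed, and the article states none.

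**Conclusion.** The mismatch is real and should be resolved. The variance comparison is the weightier half: in days, at the planned effect, Levene's test would reject in about 48% to 63–64% of trials with no difference in log-scale spread. The power loss for the comparison of time, 7 points one-sided (95% to 88%) or 10 two-sided (91% to 81%), applies only if the t test is run on days and the fallback is not used.

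These figures rest on log-normal times, a purely multiplicative effect and equal log SDs of 0.801. The last two are assumptions that the article neither states nor contradicts. With a smaller effect the confounding is smaller but remains (14% to 28% at a ratio of 0.8).

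**What to change.** In Analyses, state that the t test and the median-centred (Brown-Forsythe) form of Levene's test are run on log(time). Report the arm effect as a ratio of geometric means with a 95% CI, back-transformed to days for presentation. Say that reduced variance is interpreted on the log scale, and keep it in the primary objective: nothing here requires demoting it. Keep rank-based tests, named in advance, as sensitivity analyses rather than as a switch triggered by the data.

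This takes a few sentences and no extra participants. Under the planning assumptions it brings the t test back to the power that was calculated and Levene's test to about its nominal level. The small downside is that the main result is a ratio, which is less immediate to clinicians than a difference in days.
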